## Use of co-intervention (if applicable)

N.a.

## Escape medication (if applicable)

N.a.

INVESTIGATIONAL MEDICINAL PRODUCT

N.a.

# METHODS

## Study parameters/endpoints

### Main study parameter/endpoint

The primary objective of this study is to test the effectiveness of the intervention in terms of preventing overweight and obese children from excessive weight gain. The main study parameter is children’s body composition, determined by BMI z-score (calculated by weight, height, age and gender), waist circumference, and fat mass (assessed via biceps and triceps skinfold and deuterium). BMI, waist circumference, and skinfold is measured at baseline, 14 weeks (directly following the intervention) and 12 months follow-up. Deuterium is measured only at baseline and 12 months follow-up.

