**SUMMARY**

**Rationale:** Overweight and obesity are already prevalent in 4 to 8-year-old children. Obesity-inducing behaviours in young children have been found to track throughout the life span. Acknowledging the lack of effective interventions aimed at children aged 4 to 8-year-old, the current study aims at executing an effectiveness study in which a lifestyle intervention aimed at the parents of 4 to 8-year-old children is tested.

**Objective**: The main objective is to evaluate the effectiveness of Lifestyle Triple P.

**Study design:** The design of the current study is a Randomized Controlled Trial (RCT)

**Study population:** The research population consists of 288 participants (96 overweight and obese 4 to 8-year-old children and their parents).

**Intervention (if applicable)**: The lifestyle intervention, called Lifestyle Positive Parenting Program (Lifestyle Triple P), is aimed at parents of overweight and obese children. The intervention will take 14 weeks, consisting of eight weekly 120-minute parental group training sessions, two individual telephone sessions, one parental group training sessions, two individual telephone sessions and a final parental group training session. Triple P is an evidence-based preventively oriented parenting and family support strategy, based on social learning principles. Active skills training methods are employed to help parents acquire new knowledge and skills. The control condition receives two information leaflets (one about healthy nutrition and physical activity, and one about positive parenting), a Time Machine (an electronic screen time manager) and a web-based tailored feedback about providing a good parental example for your child regarding diet and physical activity.

**Main study parameters/endpoints:** The main study parameter is children’s body composition, determined by BMI z-score (calculated by weight, height, age and gender), waist circumference, and fat mass (assessed by biceps and triceps skinfold and deuterium dilution). Secondary study parameters are children’s lifestyle (snacking behaviour, soft-drink consumption, fruit-and vegetable consumption and physical activity), parental body composition (BMI, parental fat mass), parental physical activity level, parenting self-efficacy and parenting style.

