# OBJECTIVES

Primary Objective: The primary objective is to evaluate the effectiveness of the Lifestyle Triple P intervention in 4 to 8-year-old overweight children on their BMI z-score, and fat mass.

Secondary Objective(s): The secondary objectives of the current study are to determine the effect of the intervention on children’s lifestyle (snacking behaviour, soft-drink consumption, fruit-and vegetable consumption and physical activity), parental BMI, parental fat mass, parental physical activity level, parenting self-efficacy and parenting style.

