## Study procedures

The overweight children and their parents will undergo a set of measurements at baseline, immediately following the intervention at 14 weeks and at 12 months follow-up. The following measurements are performed (see flow chart):

- Anthropometric measurements:
  - Weight and height (child and parents) to calculate BMI and BMI z-score
  - Biceps and triceps skinfold thickness (child and parents) using the Harpenden skinfold calliper to indicate changes in fat mass
  - Waist circumference
  - Deuterium (only children) to indicate fat mass (at baseline and 6 months)
- Actigraph accelerometer (child and parents)
- Questionnaire (parents, see appendix) measuring the following constructs:
  - Demographic variables
  - Physical activity child and screen-viewing behaviour
  - Snacking behaviour, soft-drink consumption child, fruit-and vegetable consumption child
  - Children’s behaviour questionnaire measuring children’s temperament
  - Parenting practices:
    - - Child feeding behaviour questionnaire (Birch) and child physical activity behaviour
      - Parental feeding style questionnaire (Wardle)
  - Parenting self-efficacy  Being a Parent Scale
  - Parenting styles

The anthropometric measurements are conducted during a visit at the Municipal Health Service (GGD) in both parents and the child. At this visit, materials and instructions for executing deuterium dilution are distributed. Parents are instructed to collect a urine sample of their child at the evening before their child drinks deuterium enriched water. In the morning, after an overnight fast, the second morning urine should be collected as well. The urine samples are collected in small bottles, parents are asked to send them back in an envelope.

The intervention consists of ten 120-minute parental group training sessions and four individual telephone session for parents. The parental group training sessions and the individual telephone sessions will be guided by the same health educator.

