## Data Safety Monitoring Board (DSMB)

# N.a.

# STATISTICAL ANALYSIS

Primary and secondary outcome parameters will be described via descriptive statistics. Quantitative continuous variables will be presented by use of means and standard deviations. Of categorical data, percentages will be presented of respondents falling in each of the possible categories.

Both univariate and multivariate multilevel analyses (correcting for group effects) are conducted to determine the effect of the intervention on (changes in) BMI z-score, fat mass, children’s lifestyle (screen-viewing behaviour, snacking behaviour, soft-drink consumption, fruit-and vegetable consumption, and physical activity level), parenting self-efficacy, parental skills, parental BMI, parental fat mass, and parental physical activity level. In the multilevel analyses, relevant confounders such as the child’s age, gender, ethnicity and parental socio-economic status.

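### The protocol fixes no single primary outcome, time point or model, its sections disagree on waist circumference, and the sample size matches no scheduled main result

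*Protocol*

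**What the plan says.** The protocol describes the main outcome in four places, and sizes the trial in a fifth.

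- **Summary.** Body composition is the main parameter, determined by BMI z-score, "waist circumference, and fat mass (assessed by biceps and triceps skinfold and deuterium dilution").
- **Main study parameter/endpoint.** The list is the same: BMI z-score, "waist circumference, and fat mass (assessed via biceps and triceps skinfold and deuterium"). On timing: "BMI, waist circumference, and skinfold is measured at baseline, 14 weeks (directly following the intervention) and 12 months follow-up", and "Deuterium is measured only at baseline and 12 months follow-up".
- **Objectives.** The primary objective is the effect in "overweight children on their BMI z-score, and fat mass". Waist circumference and time point are not mentioned.
- **Statistical analysis.** Univariate and multivariate multilevel models are both planned "to determine the effect of the intervention on (changes in) BMI z-score, fat mass", followed in the same list by the secondary outcomes. Waist circumference is absent, and neither model is called primary.
- **Sample size calculation.** One comparison is used: 0.30 BMI-points over 6 months, power .90, p<.05, giving 38 families per arm and 96 in total after attrition.

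Study procedures gives a different time for deuterium: "Deuterium (only children) to indicate fat mass (at baseline and 6 months").

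**The concern.** A confirmatory trial needs one result, or a stated rule over several, that settles whether the intervention worked. Here the main parameter is a construct measured in four ways, three of them at two follow-up times, and nothing says how the results combine. If BMI z-score improved at 14 weeks but not at 12 months, or if skinfolds and deuterium disagreed, the protocol would not say whether Lifestyle Triple P had been effective. The choice would then be open after the data are known.

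Two further gaps follow. Waist circumference is a main parameter that neither the objective nor the analysis takes up. And the sample size, which would normally show which result the trial was built around, points to a scale and a time that are not among the main results.

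**Working it through.** **1. The outcome lists side by side**

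| Section | BMI z-score | Waist | Fat mass | Lead time | Lead model |
|---|---|---|---|---|---|
| Summary | yes | yes | skinfold and deuterium | none | not addressed |
| Main study parameter/endpoint | yes | yes | skinfold and deuterium | none | not addressed |
| Objectives | yes | no | yes, method not stated | none | not addressed |
| Statistical analysis | yes | no | yes, method not stated | none | two models, neither primary |

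There are two lists. The Summary and the endpoint section agree with each other, as do Objectives and Statistical analysis. The difference is waist circumference.

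**2. The sample-size basis**

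No SD is given, so 38 per arm cannot be reproduced, only solved backwards. For two means with 1:1 allocation, two-sided .05 (sidedness is not stated, so this is assumed) and power .90:

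SD = 0.30 / [(1.960 + 1.282) × √(2/38)] = 0.30 / 0.744 = 0.403 BMI-points.

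The implied standardised effect is 0.744. Attrition is consistent: 76/96 leaves 20.8% loss, and 38/(1 − 0.208) = 48 per arm.

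The figure is thus for one test on raw BMI over 6 months. The endpoint is BMI z-score, and BMI visits are at baseline, 14 weeks and 12 months. The calculation matches none of the scheduled main results.

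**3. How many results could count**

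- Measure by time in the endpoint section: BMI z-score 2 + waist 2 + skinfold 2 + deuterium 1 = 7.
- Without waist, as in Objectives and Statistical analysis: 2 + 2 + 1 = 5.
- One test per measure across time: 4.

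**4. False-positive chance if any one result at p<.05 were taken as success**

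The protocol does not state this rule; it is used here only to size the problem. For k independent tests the chance is 1 − 0.95^k. For correlated tests I simulated equicorrelated normal statistics (400,000 draws, two-sided .05). The correlations are assumed.

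| Tests | Independent | r=.5 | r=.7 | r=.8 | r=.9 |
|---|---|---|---|---|---|
| 4 | 18.5% | 16% | 13% | 11% | 9% |
| 5 | 22.6% | 18% | 15% | 13% | 10% |
| 7 | 30.2% | 23% | 18% | 15% | 11% |

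Running both models adds to this but does not double it, because two models of one outcome are nearly the same test. With an assumed correlation of .95 within each pair, duplicating all seven tests moves 23% to about 28–29% (r=.5) and 15% to about 18–20% (r=.8), depending on how the remaining correlations are set.

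**5. Cost of the alternatives**

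One named outcome keeps alpha at .05 and adds no families for multiplicity. Bonferroni over seven uses .05/7 = .0071. At the implied effect of 0.744, assumed equal for every outcome, that would need 58 per arm with data, or leave power of about .71 at 38 per arm.

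**The case against.** A reader might infer that the protocol plans at least seven uncorrected tests, any of which can carry the claim, with a 30% error rate. The documents do not support that. Seven is one reading of the endpoint section; the outcomes listed in the analysis section give at most five, and one test per measure gives four. The protocol is silent on multiplicity rather than declaring that none will be applied, and a correction could stand in an analysis plan that is not shown. No section says that one significant result suffices: a main parameter determined by several measures could also mean that all must agree, which would not inflate the error. The 30% needs independent tests, which is implausible for adiposity measures repeated in the same child. The protocol also undertakes to publish all results, negative ones included, which lessens selective reporting, although it does not control error.

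All of that stands, and it limits the claim about error. It does not remove the defect. A correction method may be left to an analysis plan, but which outcome is primary, and when, is for the protocol to fix. This protocol addresses the question and gives two different lists. An unseen plan cannot reconcile those sections, and the sample size does not break the tie.

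**Conclusion.** The point holds in this form: no lead outcome, time point or model is fixed; waist circumference is a main parameter without an objective or analysis; and the sample size rests on a scale and time that match no scheduled main result. These follow from the text and need no assumption.

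The effect on error is conditional, because the success rule is undefined. Under an any-one rule it would be about 9% to 23% against a nominal 5%, and 30% only as the value for seven independent tests. Even the lowest of these, four tests at r=.9, is nearly twice nominal, so the conclusion does not hang on the count of seven. The protocol's main conclusion depends on settling this before data are seen.

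**What to change.** Before data are seen:

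1. Name one primary outcome at one scheduled time from one adjusted model. BMI z-score at 12 months is one reasonable choice, not the only one. Make waist circumference, the fat-mass measures and the other time point secondary. Alternatively, state an explicit co-primary rule with its alpha.
2. Use the same wording in the Summary, Objectives, Main study parameter/endpoint and Statistical analysis, and give waist circumference a stated place in the analysis.
3. Restate the basis in Sample size calculation on the chosen outcome and time, with its SD and sidedness, without changing enrolment.
4. Reconcile the deuterium time between Main study parameter/endpoint (12 months) and Study procedures (6 months).

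The cost is mainly wording, plus one power calculation. The other measures lose primary status, and the stated power of .90 may change once it is worked out on the named outcome.

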### Secondary study parameters/endpoints (if applicable)

Secondary study parameters are parental BMI and fat mass (assessed via biceps and triceps skinfold), parenting skills, the parental self-efficacy, children’s lifestyle (screen-viewing behaviour, snacking behaviour, soft-drink consumption, F&V consumption and physical activity), and parental physical activity level. These data are assessed at baseline, 14 weeks follow-up and 12 months follow-up, via questionnaires, and the Actigraph accelerometers.

### Other study parameters (if applicable)

The following study parameters are taken into account as confounders: SES, ethnicity, and children’s temperament, which are all measured in a baseline questionnaire.

## Randomisation, blinding and treatment allocation

Block randomisation (n = 4) will be performed on the individual level. After parents of four families decide to participate in the study, they will be randomised to either the experimental condition or the control condition.

## Study procedures

The overweight children and their parents will undergo a set of measurements at baseline, immediately following the intervention at 14 weeks and at 12 months follow-up. The following measurements are performed (see flow chart):

- Anthropometric measurements:
  - Weight and height (child and parents) to calculate BMI and BMI z-score
  - Biceps and triceps skinfold thickness (child and parents) using the Harpenden skinfold calliper to indicate changes in fat mass
  - Waist circumference
  - Deuterium (only children) to indicate fat mass (at baseline and 6 months)
- Actigraph accelerometer (child and parents)
- Questionnaire (parents, see appendix) measuring the following constructs:
  - Demographic variables
  - Physical activity child and screen-viewing behaviour
  - Snacking behaviour, soft-drink consumption child, fruit-and vegetable consumption child
  - Children’s behaviour questionnaire measuring children’s temperament
  - Parenting practices:
    - - Child feeding behaviour questionnaire (Birch) and child physical activity behaviour
      - Parental feeding style questionnaire (Wardle)
  - Parenting self-efficacy  Being a Parent Scale
  - Parenting styles

The anthropometric measurements are conducted during a visit at the Municipal Health Service (GGD) in both parents and the child. At this visit, materials and instructions for executing deuterium dilution are distributed. Parents are instructed to collect a urine sample of their child at the evening before their child drinks deuterium enriched water. In the morning, after an overnight fast, the second morning urine should be collected as well. The urine samples are collected in small bottles, parents are asked to send them back in an envelope.

The intervention consists of ten 120-minute parental group training sessions and four individual telephone session for parents. The parental group training sessions and the individual telephone sessions will be guided by the same health educator.

## Withdrawal of individual subjects

Subjects can leave the study at any time for any reason if they wish to do so without any consequences. The investigator can decide to withdraw a subject from the study for urgent medical reasons.

### Specific criteria for withdrawal (if applicable)

N.a.

## Replacement of individual subjects after withdrawal

N.a.

## Follow-up of subjects withdrawn from treatment

N.a.

## Premature termination of the study

N.a.

# SAFETY REPORTING

## Section 10 WMO event

In accordance to section 10, subsection 1, of the WMO, the investigator will inform the subjects and the reviewing accredited METC if anything occurs, on the basis of which it appears that the disadvantages of participation may be significantly greater than was foreseen in the research proposal. The study will be suspended pending further review by the accredited METC, except insofar as suspension would jeopardise the subjects’ health. The investigator will take care that all subjects are kept informed.

## Adverse and serious adverse events

Adverse events are defined as any undesirable experience occurring to a subject during the study, whether or not considered related to [the investigational product / the experimental treatment]. All adverse events reported spontaneously by the subject or observed by the investiga­tor or his staff will be recorded.

A serious adverse event is any untoward medical occurrence or effect that at any dose:

- results in death;
- is life threatening (at the time of the event);
- requires hospitalisation or prolongation of existing inpatients’ hospitalisation;
- results in persistent or significant disability or incapacity;
- is a congenital anomaly or birth defect;
- is a new event of the trial likely to affect the safety of the subjects, such as an unexpected outcome of an adverse reaction, lack of efficacy of an IMP used for the treatment of a life threatening disease, major safety finding from a newly completed animal study, etc.

All SAEs will be reported through the web portal *ToetsingOnline* to the accredited METC that approved the protocol, within 15 days after the sponsor has first knowledge of the serious adverse reactions.

SAEs that result in death or are life threatening should be reported expedited. The expedited reporting will occur not later than 7 days after the responsible investigator has first knowledge of the adverse reaction. This is for a preliminary report with another 8 days for completion of the report.

### Suspected unexpected serious adverse reactions (SUSAR)

N.a.

### Annual safety report

N.a.

## Follow-up of adverse events

N.a.

## Data Safety Monitoring Board (DSMB)

# N.a.

# STATISTICAL ANALYSIS

Primary and secondary outcome parameters will be described via descriptive statistics. Quantitative continuous variables will be presented by use of means and standard deviations. Of categorical data, percentages will be presented of respondents falling in each of the possible categories.

Both univariate and multivariate multilevel analyses (correcting for group effects) are conducted to determine the effect of the intervention on (changes in) BMI z-score, fat mass, children’s lifestyle (screen-viewing behaviour, snacking behaviour, soft-drink consumption, fruit-and vegetable consumption, and physical activity level), parenting self-efficacy, parental skills, parental BMI, parental fat mass, and parental physical activity level. In the multilevel analyses, relevant confounders such as the child’s age, gender, ethnicity and parental socio-economic status.

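### The protocol leaves open whether the response is change or follow-up and does not name the baseline outcome as a covariate, so it permits a less precise estimate than the data allow

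*Protocol*

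**What the plan says.** The Statistical analysis section of the Protocol describes the models in one sentence, which begins: "Both univariate and multivariate multilevel analyses (correcting for group effects) are conducted to determine the effect of the intervention on (changes in) BMI z-score". It goes on to list fat mass, the child's lifestyle measures, and the parenting and parental outcomes. The word for change stands in brackets, so the response may be a change score or a follow-up value.

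The next sentence names "relevant confounders such as the child’s age, gender, ethnicity and parental socio-economic status". It has no main verb, and its list is given as examples. The section Other study parameters adds: "The following study parameters are taken into account as confounders: SES, ethnicity, and children’s temperament, which are all measured in a baseline questionnaire". Neither place mentions the baseline value of the outcome.

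That value is available. For the main parameter: "BMI, waist circumference, and skinfold is measured at baseline, 14 weeks (directly following the intervention) and 12 months follow-up", and "Deuterium is measured only at baseline and 12 months follow-up". (Study procedures gives 6 months for the second deuterium measurement, but baseline is common to both statements.) For the secondary parameters: "These data are assessed at baseline, 14 weeks follow-up and 12 months follow-up, via questionnaires, and the Actigraph accelerometers". The Study design section and Flow chart 1 both place randomisation after the baseline measurements.

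**The concern.** The baseline value of an outcome is usually its strongest single predictor. Here it is measured in any case, yet it is missing from both places where the protocol names covariates.

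Two things are at stake. The first is precision: a difference in mean change, or in mean follow-up value, generally has a larger variance than the same comparison adjusted for baseline. The second is behaviour when the arms happen to differ at baseline. There are 48 families per arm. Inclusion covers both overweight and obese children. The Randomisation section describes blocks of four and names no stratification factor, so nothing described there balances baseline BMI. A change score over-corrects a chance imbalance, and an unadjusted follow-up value leaves it in.

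**Working it through.** **The plan's own figure.** The sample size section asks for 38 families per condition to detect 0.30 BMI points with power 0.90 at p < .05. It gives no SD, so 38 cannot be reproduced independently. Solving backwards with the two-sided normal formula gives SD = 0.30 / ((1.960 + 1.282) × √(2/38)) = 0.403 BMI points. With an assumed 20% loss, 38 / 0.80 = 47.5, rounded up to 48 per arm or 96 in total, as stated. Nothing here shows the sample size to be wrong. The SD of 0.403 is used below only to express the gain as power.

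**Variance of the three estimators.** Assume the same SD, σ, at baseline and follow-up, correlation r between them, n per arm, and no clustering. In units of 2σ²/n:

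- follow-up value alone: 1
- change score: 2(1 − r)
- follow-up adjusted for baseline: 1 − r²

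Adjusted against change, the ratio is (1 − r²) / (2(1 − r)) = (1 + r)/2. Adjusted against follow-up alone, it is 1 − r². The protocol does not give r, so a range is shown.

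| r (assumed) | Change score | Adjusted | Reduction v. change | Reduction v. follow-up alone |
|---|---|---|---|---|
| 0.5 | 1.00 | 0.75 | 25% | 25% |
| 0.7 | 0.60 | 0.51 | 15% | 49% |
| 0.8 | 0.40 | 0.36 | 10% | 64% |
| 0.9 | 0.20 | 0.19 | 5% | 81% |

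**In terms of power.** Suppose 0.403 is the SD of change. The variance is then multiplied by (1 + r)/2. At 38 per arm, power rises from 0.90 to 0.963 (r = 0.5), 0.940 (0.7), 0.927 (0.8) or 0.914 (0.9). Equivalently, 29, 33, 35 or 37 per arm would give the power that 38 give now. These figures are in BMI points, as in the sample size section, whereas the modelled outcome is BMI z-score; they illustrate the size of the gain only.

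**Sensitivity to imbalance.** The chance difference between arms at baseline has standard error σ√(2/48) = 0.204σ with all families, and σ√(2/38) = 0.229σ with 38 per arm. Given an observed baseline difference D, the expected shift in the estimate is −(1 − r)D for a change score, rD for follow-up alone, and 0 after linear adjustment for baseline. For D = 0.20σ, about one standard error:

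| r (assumed) | Change score | Follow-up alone |
|---|---|---|
| 0.5 | −0.10σ | +0.10σ |
| 0.8 | −0.04σ | +0.16σ |
| 0.9 | −0.02σ | +0.18σ |

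**The case against.** The strongest reply is that the protocol is silent rather than wrong. A reader might infer that the planned models leave baseline out. The text does not support that: the covariates are given as examples, the sentence is unfinished, and nothing rules baseline out. A multilevel model with baseline as one of the repeated measurements would also use it. This stands, and it limits the point to what the wording permits. (A repeated-measures model gains the precision shown only if the arms share one baseline mean. With separate baseline means, complete data and an unstructured covariance, its contrast is the change-score estimate again.)

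A reader might also take the 64% and 81% reductions as the cost of the plan. They apply only to unadjusted follow-up values, which the text does not clearly plan; its mention of change points the other way. Against a change score, the gain at high r is 5% to 10%.

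Nor does the text support a claim of bias. Under randomisation, change scores and follow-up values both estimate the treatment effect without bias. What remains is precision, and bias conditional on an observed imbalance.

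The two lists of confounders differ, since temperament appears in only one and age and gender only in the other. As one list is open-ended it can hold temperament, so this is not a firm contradiction. Which of the univariate and multivariate analyses decides, and the full covariate set, may properly be left to a statistical analysis plan that is not shown.

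Finally, the Randomisation section ties allocation to four families agreeing to take part and does not mention completed baseline measurements. Accelerometers are worn for seven days and deuterium samples are mailed back afterwards. A child's objection can also stop a measurement. Some baseline values may therefore be late or missing. That calls for care in the analysis, but the Study design section and Flow chart 1 still state that baseline comes first.

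**Conclusion.** The point holds as a matter of efficiency and clarity, not of validity. The protocol does not settle the form of the response and does not name the baseline outcome as a covariate. Followed as written, it permits an estimate that is less precise than the collected data allow and that moves with chance baseline imbalance.

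Against a change score the loss is modest for outcomes that track closely (5% of variance at r = 0.9, 10% at 0.8) and larger for those that do not (25% at 0.5). Lower correlations are more plausible for the diet, activity and parenting scores than for BMI z-score, but that is an assumption. The figures rest on equal variances at the two times, an assumed r, and no allowance for clustering by training group. The protocol gives neither r nor an SD, so the gain in this trial cannot be fixed more closely.

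**What to change.** In the Statistical analysis section, state that the primary model for each outcome takes the follow-up value as the response, with arm and the baseline value of the same outcome as fixed effects, within the planned multilevel model and alongside the covariates the protocol already names. Report the model without covariates as a sensitivity analysis.

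This needs no new data and no change to visits or sample size. It costs about one degree of freedom per model and a few lines of text. It should be settled before outcome data are examined by arm.
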